### Specific inclusion criteria for the “Smoking Cessation” RCT

Only people who smoke at baseline (t0) can take part in the “Smoking Cessation” online RCT.

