**Primary**^**i**^**and secondary**^**ii**^**Outcomes**							
Weight	IRES [48]/Changes in mean kilogram	**W**^**i**^,F^**ii**^,S^ii^	1	**x**	**x**	**x**	**x**
Physical activity	Physical Activity and Sport Activity Questionnaire (BSA-F 3.0) [51]/Changes in mean score	W^ii^,**F**^**i**^	17	**x**	**x**	**x**	**x**
Smoking abstinence in the last 30 days	Self –developed/Changes in percentages (dichotomous data)	**S**^**i**^	1	**x**	**x**	**x**	**x**
Health related goal intention	Goal intention [52] [53]; adapted/Differences of mean values	W^ii^,F^**ii**^,S^ii^	1	**x**	**x**	**x**	**x**
Sport- and movement-related self-concordance	Sport- and movement-related self-concordance [54]/Changes in mean score	F^ii^	12	**x**	**x**	**x**	**x**
Self-efficacy (dietary)	Testing phase-specific self-efficacy [55]/Changes in mean score	W^ii^	7	**x**	**x**	**x**	**x**
Self-efficacy (smoking)	Scales for the measurement of self-efficacy and decisional balance in the process of behavioral change in smokers [56]/Changes in mean score	S^ii^	9	**x**	**x**	**x**	**x**
Barrier management in physical exercise	Barriers and barrier management in physical exercise [57]/Changes in mean score	F^ii^	29	**x**	**x**	**x**	**x**
Expectation of consequences	BRAHMS [50]; adapted/Changes in mean score	W^ii^, S^ii^	18	**x**	**x**	**x**	**x**
Action planning	Action plans and coping plans for physical exercise [58]/Changes in means score	F^ii^	13	**x**	**x**	**x**	**x**
Risk perception	Risk perceptions of cigarettes and e-cigarettes [59]; adapted/Changes in mean score	S^ii^	5	**x**			
Perceived goal attainment	Self-developed/Differences in means	W^ii^,F^ii^,S^ii^	2		**x**	**x**	**x**
Eating behavior German Eating Behavior Scale	German Eating Behavior Scale (SEV)*;article submitted [21]/Changes in mean score	W^ii^, F^ii^	32	**x**	**x**	**x**	**x**
Nicotine dependence	Fagerstrom Tolerance Questionnaire *(*FTND [60])/Changes in mean score	S^ii^	6	**x**	**x**	**x**	**x**
Health-related quality of life	Short Form 12 Health Survey (SF-12) [61]/Changes in mean score	W^ii^,F^ii^,S^ii^	12	**x**	**x**	**x**	**x**

Health goals: W=”Losing and Maintaining Weight”; F=”Increasing Fitness”, S=” Smoking Cessation”

Measurement time point: t0 = baseline, t1 = first follow-up; t2 = second follow-up; t3 = third follow-up; IRES = indicators of rehabilitation status

Primary outcome of the related health goals; highlighted in bold

Secondary outcomes of the related health goals

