**Confounder**							
Mental illness	Patient Health Questionnaire (PHQ-2 [62])/mean score One self-developed item/dichotomous	W, F, S	3	**x**	**x**	**x**	**x**
Health impairments	Comorbidity Score (KoMo) [32]/mean score	W, F, S	24	**x**			
General state of health	BRAHMS [50]; adapted	W, F, S	1	**x**			
Addictive substances other than tobacco (s)	Alcohol, Smoking and Substance Involvement Screening Test (WHO-ASSIST), question N°2 [63] ; three of ten items: alcohol, cannabis, sedatives and sleeping pills/value of each Item	S	3	**x**	**x**	**x**	**x**
Social support	The weigh-related interactions Scale (WRIS) [26]; adapted/mean score	W	14	**x**	**x**	**x**	**x**
	Social support [64] (in prep.)/mean score	F	12	**x**	**x**	**x**	**x**
	Partner Interaction Questionnaire (PIQ-20 [65]); adapted/mean score	S	17	**x**	**x**	**x**	**x**

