Possible covariates (see Table 4) will enter the model at level 1 (X) when they are measured at more than one time point or at level 2 (Z) when they are only measured at baseline. The covariates differ in type and number between the three coaches. The components X and Z are therefore only placeholders. The covariates considered may represent real-life conditions of participants existing independently of the program; they can be beneficial or detrimental to participants’ goal attainment or outcomes. The social environment in particular may be conducive or an obstacle [26–30]. The importance of social and emotional support from people, who are close, is also pointed out by the NICE guideline *Behaviour Change: individual approaches* [31]. Tiredness and a decrease in drive and activity are indications of mood disorders. Self-efficacy, motivation and intention to change, as well as functional or physical limitations are predictors for behavioral change and associated with mental health, health status, and comorbidities [32–40]. Furthermore, it is likely that additional addictive behaviors and low degree of mental health will make smoking cessation more difficult [33, 41, 42]. Since past behavior predicts future behavior, as confirmed in a meta-analysis [43], preconditions such as mental health, health status comorbidity, additional addictive behavior, but also social support, assessed at baseline, are considered as program-independent covariates of primary outcomes. We use these covariates, along with sex, age, and primary outcome at baseline to adjust the statistical models in the analyses. In these models, coefficient *γ*_10_ refers to the change over time of the intervention groups (hypothesis 1), while coefficient *γ*_11_ refers to the difference in change between intervention and control group (hypothesis 2).

For the analyses of secondary outcomes, measuring mean changes over time (see Table 3), we use linear mixed models analogous to the primary outcomes in weight loss and fitness. Differences between intervention and control groups in for example “Health related goal intention” or “Perceived goal attainment” will be analyzed using *t* tests.

To test the dose-effect association (hypothesis 3), the outlined model will be adapted—here, we only use the intervention group, so the group variable will be dropped. Instead of the group variable, a variable that code the use (e.g., number of logins) of the coach will enter the model at level 2.

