All metric covariates at level 1 will be group mean-centered, while metric covariates at level 2 will be grand mean-centered. Categorical variables enter as dummy-coded (0/1) variables.

Post-hoc analyses with correction for multiple testing will be conducted to identify changes between specific time points to analyze short-term effects, e.g., between t0 and t1. As effect size, with their 95% confidence intervals, we will calculate Cohen’s *d* bases on the *t* values from the pairwise comparisons from the LMM respective odds ratio for the GLMM.

In the case of the *SmokingCessationCoaching*, we will drop the baseline (T0) from the model, because every case concerns smoking. It is, therefore, not possible to calculate the odds ratio for the change between baseline and post-intervention. Instead, we will use the difference in smoking cessation at post intervention between both groups as the effect size.

Furthermore, we will apply structural equation modeling to test various models for assessing potential mediators of the intervention effect on outcomes.

The analyses are carried out according to the intention-to-treat principle (ITT). In ITT, all randomized participants will be considered in the main analyses. In per-protocol analyses (PP), only those participants will be included who have been randomized, have participated at all time points, and filled out corresponding primary outcomes. The randomization condition for study participants was that they accessed the program at least once.

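### In the smoking RCT the planned baseline-outcome covariate is a constant, and the nicotine dependence score collected at t0 is not named in its place

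*Protocol article*

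**What the plan says.** The Summative evaluation section describes one adjustment strategy for all three RCTs. It points to Table 4 for candidate covariates and describes them as "preconditions such as mental health, health status comorbidity, additional addictive behavior, but also social support, assessed at baseline". It then states: "We use these covariates, along with sex, age, and primary outcome at baseline to adjust the statistical models in the analyses". It motivates this by the finding that earlier behaviour predicts later behaviour. It also notes that "The covariates differ in type and number between the three coaches".

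For the smoking RCT:

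- The primary outcome is 30-day abstinence, yes or no (Table 3).
- The specific inclusion criterion reads "Only people who smoke at baseline (t0) can take part". The matching exclusion criterion rules out anyone who has already stopped, even very recently.
- The analysis section adds that "we will drop the baseline (T0) from the model, because every case concerns smoking". It takes the post-intervention difference in cessation between the groups as the effect size, without fixing its scale.
- Nicotine dependence ("Fagerstrom Tolerance Questionnaire", 6 items, t0 to t3) is listed in Table 3 as a secondary outcome. It is not in Table 4, whose addiction item covers alcohol, cannabis, and sedatives or sleeping pills, and excludes tobacco.

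Under Sensitivity analysis and missing values, the ITT analysis imputes outcomes and predictors by multiple imputation if data are missing at random or completely at random. The variables that the imputation model conditions on are not listed.

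**The concern.** In the weight and fitness RCTs, adjusting for the baseline outcome brings in a measured starting level. In the smoking RCT the same term cannot vary. The smoking model as described would therefore adjust for other addictive substances but for no baseline measure of tobacco use, against the plan's own reason for adjusting.

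Two things could be at stake. One is a little precision. The other is missing outcomes: the article assumes 50% dropout. If more dependent smokers both quit less and answer less, and if no model conditions on dependence, abstinence among responders is higher than among all randomised participants.

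**Working it through.** **1. The plan's own figure.** At 15% vs 2% with two-sided alpha 0.05, full enumeration of Fisher's exact test gives power 79.4% at 76 per arm and 80.1% at 77 per arm. So 77 is reproduced. Then 77 / 0.5 = 154 per arm, and (154 + 154) x 1.1 = 338.8, i.e. 339. Nothing below changes these numbers.

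**2. The constant.** Every participant smokes at t0, so the baseline-outcome column equals a fixed value for all. A design matrix with an intercept, this column and the group indicator has rank 2 out of 3 columns. Software drops the column or merges it with the intercept; it neither adjusts for anything nor distorts the group effect.

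**3. Chance imbalance and precision.** With a standardised score, the SD of the arm difference in mean dependence is sqrt(2/n): sqrt(2/77) = 0.16 SD, and sqrt(2/85) = 0.15 SD (85 being about 339 / 2 x 0.5). This is random and already covered by the test's error rate. In 2,000 simulated null trials (15% in both arms, 154 randomised per arm, 50% dropout unrelated to dependence, assumed log odds ratio for abstinence -0.5 per SD), type I error was 4.7% unadjusted and 4.6% adjusted. The power gain was small:

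| Simulation at 15% vs 2% | Unadjusted | Adjusted |
|---|---|---|
| 85 per arm, abstinence OR 0.7 per SD | 91.8% | 91.8% |
| 85 per arm, abstinence OR 0.5 per SD | 91.8% | 92.1% |
| 154 randomised per arm, 50% dropout, log OR -0.5 per SD (trials with at least one abstainer in each arm) | 78.1% | 79.3% |

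**4. Dropout related to dependence, equal in both arms.** Inputs from the article: 15%, 2% and 50% dropout. Assumed, not in the article: X is a standard normal dependence score, the abstinence odds ratio is 0.5-0.7 per SD, and the response slope d is -0.3 to -0.8. These slopes mean about 56-65% response in the less dependent half and 44-35% in the more dependent half.

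- P(abstinent | X) = expit(a + bX), with a solved so that the average over X is 15% or 2%.
- P(response | X) = expit(dX), which averages 50%.
- Abstinence among responders = E[P(abstinent | X) x P(response | X)] / E[P(response | X)].

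| OR per SD | d | Intervention | Control | Difference (points) | Odds ratio |
|---|---|---|---|---|---|
| 0.7 | -0.3 | 15.7% | 2.1% | 13.6 | 8.64 |
| 0.7 | -0.5 | 16.1% | 2.2% | 13.9 | 8.65 |
| 0.7 | -0.8 | 16.6% | 2.2% | 14.3 | 8.65 |
| 0.5 | -0.3 | 16.2% | 2.2% | 14.0 | 8.62 |
| 0.5 | -0.5 | 17.0% | 2.3% | 14.6 | 8.62 |
| 0.5 | -0.8 | 17.9% | 2.5% | 15.4 | 8.63 |

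Differences are computed before rounding. The true values are 13.0 points and (0.15/0.85) / (0.02/0.98) = 8.65. Both rates rise, so the absolute difference grows by 0.6-2.4 points while the odds ratio hardly moves. With no true effect the two arms have the same responder rate, so a null stays null.

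**5. Dropout related to dependence, different by arm.** Here the log odds ratio for abstinence is -0.3 to -0.8 per SD, and the dropout slopes range from 0.5 vs 0 to +0.5 vs -0.5, in either direction. With a true null at 15%, the unadjusted odds ratio becomes 1.07-1.42 or 0.71-0.93, a spurious 0.9-4.4 points. At -0.5 per SD with slopes +0.5 vs -0.5, simulated type I error is 6.8% unadjusted and 3.9% adjusted.

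**The case against.** The adjustment sentence is general text for three RCTs, and the smoking-specific sentence shows that the authors saw that t0 does not vary. The covariate list is also partly open: it is introduced by examples, called possible, and said to differ between programmes. Both points stand as far as they go. But the smoking-specific sentence only removes t0 and puts nothing in its place. The list refers to Table 4 and then says that these covariates are used, and dependence is in neither place. This is a stated term that is empty in one trial, not merely detail left to a later document.

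A reader might infer more than the article supports:

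- *That imbalance in dependence biases the comparison.* Under randomisation it is chance, and step 3 shows no effect on type I error.
- *That the imputation leaves dependence out.* The article says which variables are imputed, not which ones the imputation model uses. The score is itself a secondary outcome, so its inclusion is compatible with the text.
- *That the treatment effect is overstated even with equal response behaviour.* This is true only of the absolute difference. The planned model is a GLMM with odds ratios, on which the effect and its test are essentially untouched. The absolute scale matters because the post-intervention difference is named as the effect size with no scale given.

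The illustration in step 4 also gives no credit to the planned covariates or to earlier abstinence reports, so for its assumed values it leans towards the upper end. Dropout that differs by arm is plausible with unblinded arms of different intensity, but the article does not establish it.

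**Conclusion.** The point holds as a free improvement, not as a demonstrated bias. The baseline-outcome term is empty in the smoking RCT, and no baseline smoking-severity covariate replaces it, although one is collected at t0. The certain cost is at most about one point of power. The possible cost is an absolute difference of 13.6-15.4 points against a true 13.0. It arises only if dependence predicts both quitting and response at the assumed strengths and is in neither the analysis nor the imputation model. The odds ratio and type I error are at risk only if, in addition, dependence-related dropout differs between the arms.

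**What to change.** For the smoking RCT, replace the baseline primary outcome in the adjustment set by the t0 nicotine dependence score, entered at level 2 and grand-mean-centred like the other metric level-2 covariates. Name the same score as a predictor in the imputation model. The second half is what would protect an absolute difference; the first gives an odds ratio conditional on dependence and should be reported as such.

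The cost is one or two sentences in the analysis plan. The score is already collected, and 77, 154 and 339 are unchanged. Because the constant contributes nothing, the swap in effect adds one estimated parameter. With 77 per arm, about 0.15 x 77 + 0.02 x 77 = 13 abstainers are expected at a time point, so the score should take priority over weaker covariates.

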### Research questions and hypothesis

The following questions and hypotheses are being investigated in this study
What effects do the online programs within the three health goals *Losing and Maintaining Weight*, *Increasing Fitness*, and *Smoking Cessation* have on the primary and secondary outcomes variables reported by participants?We assume that we will observe statistically significant improvements with small to medium effect sizes for each program.Will the intervention groups (interactive health programs) in each RCT reveal stronger effects on primary and secondary outcomes in comparison to the control groups (non-interactive health programs)? We will test the hypothesis that the intervention groups’ changes in the primary and secondary outcomes are more positive than the control groups’. Our focus is on long-term effects so we will analyze the change between baseline (t0) and 1 year after the intervention finishes (t3), while short-term effects are part of the secondary analyses. We expect small to medium effect sizes from the comparison between these two groups.Does the intensity of use of health programs have an impact on their effects?The hypothesis we test is that study participants who use their health program more frequently and intensively achieve better outcomes than study participants who use the program less often or less intensively.How satisfied with the programs offered are the study participants in the intervention- and control groups? This question will be examined exploratively in secondary analyses.

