### Study outcomes and data analyses

#### Summative evaluation

Our four major research questions for this project are illustrated above.

We will use a linear mixed model (LMM) for the primary outcomes weight loss (kilogram) and fitness (BSA-Score), and for the outcome smoking cessation, we use a generalized linear model (GLMM) because of the dichotomous outcome variable (Smoking yes/no). The cluster variable is the person-id (level 2-group variable) with the time point nested within it (level 1 measurement), that permits us to model individual and group level changes [23–25]. For each primary outcome, we apply the following basic model with cross-level interaction and random slopes:

Level 1: *Outcome* = *β*_0*j*_ + *β*_1*j*_ ∗ *time* + *β*_*nj*_ ∗ *X*_*nj*_ + *r*_*ij*_

Level 2: *β*_0*j*_ = *γ*_00_ + *γ*_01_ ∗ *group* + *γ*_0*n*_ ∗ *Z*_0*n*_ + *u*_*oj*_
$$ {\beta}_{1j}={\gamma}_{10}+{\gamma}_{11}\ast group+{u}_{1j} $$

“Group” will be a dichotomous variable, which contrasts the intervention group vs. the control group. ’Time’ consists of four time points coded with 0 to 3.

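### γ10 cannot test hypothesis 1 in the smoking model once t0 is dropped, and in the weight and fitness models it does so only if the unstated reference arm is the intervention arm

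*Protocol article*

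**What the plan says.** All references are to the protocol article.

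- **Research questions and hypothesis.** Hypothesis 1 concerns improvement under the programmes: "We assume that we will observe statistically significant improvements with small to medium effect sizes for each program". Hypothesis 2 is the comparison between arms.
- **Summative evaluation, model.** One basic model is given for every primary outcome: a linear mixed model for weight and fitness, and a generalised one for smoking. The level-2 slope is β1j = γ10 + γ11·group + u1j. The group variable "will be a dichotomous variable, which contrasts the intervention group vs. the control group", and time "consists of four time points coded with 0 to 3".
- **Summative evaluation, coefficients.** For these models, without exception, γ10 "refers to the change over time of the intervention groups (hypothesis 1", and γ11 "refers to the difference in change between intervention and control group (hypothesis 2".
- **Summative evaluation, coding.** "Categorical variables enter as dummy-coded (0/1) variables". The arm that takes the value 0 is not named.
- **Summative evaluation, smoking.** "we will drop the baseline (T0) from the model, because every case concerns smoking". The effect size there becomes the between-arm difference in cessation after the programme. Neither γ10 nor hypothesis 1 is redefined for this model.

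**The concern.** In a model with a time-by-group interaction, the main time coefficient is the slope of the arm coded 0, over whatever visits remain in the model. The article gives this coefficient a fixed meaning, the intervention group's change, and ties hypothesis 1 to it. Two features of the plan disturb that meaning.

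First, hypothesis 1 is about improvement from the start of the programme, but the smoking model no longer contains the start. A slope fitted to t1, t2 and t3 cannot see the move from smoking to abstinence, which happens between t0 and t1.

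Second, an analyst who uses the common coding (control = 0) in the weight and fitness models and follows the article literally would report the control group's trend as the intervention group's result.

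At stake is the answer to hypothesis 1. For smoking, a programme that worked could appear to have had no effect or a harmful one.

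**Working it through.** No figure in the article depends on γ10, so there is none to reproduce.

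**Smoking model**

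Inputs:
- Abstinence at t0 is 0%, because only current smokers are eligible (specific inclusion criteria for the smoking RCT).
- Planned abstinence is 15% with intervention and 2% with control (Table 5). Table 5 gives no time point, so I hold these rates constant over t1–t3.
- The relapse path of 25%, 20%, 15% is my assumption, for illustration.

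With three equally coded steps, the least-squares slope of the logit is (logit p at t3 − logit p at t1) / 2.

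| Intervention arm, t1 / t2 / t3 | Slope per step | Odds ratio per step |
|---|---|---|
| 15 / 15 / 15% (planned rate, sustained) | (−1.735 + 1.735) / 2 = 0 | 1.00 |
| 25 / 20 / 15% (assumed relapse) | (−1.735 + 1.099) / 2 = −0.318 | 0.73 |

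The control arm also has slope 0 if its 2% is sustained, so the coding of group does not matter here. Renumbering the visits does not help either: it moves the intercept and leaves the slope as it is. The level of abstinence sits in the intercept terms γ00 and γ01, not in γ10.

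These are slopes of the observed proportions. A mixed model with person-level effects would give a different size, but it would cover the same t1–t3 window.

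**Weight and fitness models**

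Put the two codes into the level-2 equation:
- slope at group = 0: γ10
- slope at group = 1: γ10 + γ11

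As a check, one data set was simulated with 506 per arm, times 0 to 3, random intercepts and slopes, and assumed true slopes of −0.30 (intervention) and −0.10 (control).

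| Coding | γ10 | γ11 | γ10 + γ11 |
|---|---|---|---|
| Intervention = 1, control = 0 | −0.106 (control slope) | −0.212 | −0.318 (intervention slope) |
| Intervention = 0, control = 1 | −0.318 (intervention slope) | +0.212 (control minus intervention) | −0.106 (control slope) |

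That −0.318 appears in both tables is coincidence. The article's sentence on γ10 matches the second coding only. The size of γ11 is the same under both, and only its sign changes.

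**The case against.** The strongest reply concerns weight and fitness. A reader might infer that the plan reads the wrong coefficient in all three trials. The document does not show that. It never names the arm coded 0, and with intervention = 0 its sentence is correct. Its description of γ11 gives no direction, so the reversed sign contradicts nothing, and a two-sided test is unchanged. Effect sizes for these outcomes also come from pairwise comparisons between time points, so γ10 is not the only measure of change reported. All of this stands. What remains is an unstated reference arm, in a plan that attaches a hypothesis to a coefficient whose meaning depends on it.

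For smoking, one can reply that the article recognises that no odds ratio from baseline can be calculated and supplies another effect size. That is true, but the substitute compares the arms. It answers hypothesis 2 and gives hypothesis 1 nothing.

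Three further inferences go too far:

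- **The smoking slope must be negative.** It is zero if abstinence is sustained and positive if people quit late. The article also describes the variable as smoking yes/no; if smoking is coded 1, relapse gives a positive slope.
- **Hypothesis 1 must cover both arms.** Each programme may mean the three health goals, and the sentence on γ10 speaks of the intervention groups only.
- **A within-arm change will be presented as effectiveness.** That predicts how results will be reported. The stated aim is the comparison of interactive with non-interactive programmes.

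**Conclusion.** The point holds fully for smoking and conditionally for weight and fitness.

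In the smoking trial, γ10 as defined gives no valid answer to hypothesis 1 under either coding of the arms. It is 0 at a sustained 15% and indicates worsening under relapse, although every abstinent participant is a gain on 0% at baseline. The zero rests on holding the Table 5 rate constant, and the −0.318 on an assumed path. That the slope omits the t0–t1 change rests on neither.

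In the weight and fitness trials the defect is the unnamed reference arm. Whether the wrong slope would be read depends on a coding that the article does not give. The randomised comparison of hypothesis 2 for these two outcomes is unaffected apart from the sign of γ11.

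This should be corrected before analysis. It does not threaten the between-arm conclusions for weight and fitness.

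**What to change.** - **Smoking.** Stop using γ10 for hypothesis 1. Use the proportion abstinent at t3 in each arm, with a 95% confidence interval.
- **Weight and fitness.** State control = 0 and intervention = 1. Test hypothesis 1 for the intervention arm by the contrast γ10 + γ11. If hypothesis 1 is also meant to cover the control programme, say so and use γ10 for it. With this coding γ11 is intervention minus control.
- **Text.** Correct the sentence that assigns γ10 to the intervention groups, and except the smoking model from it.

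The cost is one linear contrast in each of the weight and fitness models, two proportions for smoking, and a few changed sentences. No new data are needed, and the sample size is unaffected.

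### Health-related goal intention is measured at t0 to t3 in all three RCTs but is assigned a between-group t test that, as naturally read, does not use its baseline value

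*Protocol article*

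**What the plan says.** The Summative evaluation section sets two methods for secondary outcomes. The general one is: "For the analyses of secondary outcomes, measuring mean changes over time (see Table 3), we use linear mixed models analogous to the primary outcomes". The sentence after it opens "Differences between intervention and control groups in for example", names two outcomes and gives the method: "Health related goal intention” or “Perceived goal attainment” will be analyzed using *t* tests". It does not say which time point is tested, whether raw or change scores are compared, or whether the baseline value enters.

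Table 3 lists goal intention for all three health goals, with marks at t0, t1, t2 and t3, and describes its analysis as "Goal intention [52] [53]; adapted/Differences of mean values". Perceived goal attainment has the entry "Self-developed/Differences in means" and marks at t1, t2 and t3 only.

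The Research questions and hypothesis section states the comparison for all outcomes as one of change, namely that "the intervention groups’ changes in the primary and secondary outcomes are more positive than the control groups". It puts the focus on the period from baseline to t3.

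**The concern.** The two outcomes given t tests are not alike. Perceived goal attainment cannot have a baseline, so a comparison at follow-up without one is the only choice. Goal intention has a baseline in every RCT, collected with the same single item as the follow-up values.

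Goal intention is also the only row of Table 3 with marks at all four time points whose analysis is not described as a change. Its label is close to that of perceived goal attainment. The natural reading is therefore that group means at follow-up are compared and the t0 value is not used.

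Two things are at stake. First, the test would not match the article's own hypothesis, which is a difference in change from t0 to t3. Second, it would give up precision that the collected baseline could supply, in all three RCTs.

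**Working it through.** **Inputs from the article (Sample size calculation, Table 5).** Two-sided alpha 0.05, power 0.80, effect size 0.25 for physical activity, 253 per arm for the fitness and weight RCTs, 77 per arm for the smoking RCT, 50% dropout. Allocation is equal.

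**Inputs assumed.** The article gives no effect size for goal intention and no correlation r between its t0 and t3 values. I borrow d = 0.25 from physical activity and take r = 0.3, 0.5 and 0.7, with equal SDs at both times (set to 1).

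**Step 1: reproduce the plan's figure.** n per arm = 2 × (1.960 + 0.842)² / 0.25² = 251.2, rounded up to 252. The t-distribution solution is 252.13, rounded up to 253, which agrees with Table 5. With 50% dropout, 253 / 0.5 = 506, which also agrees. No stated figure is in dispute.

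**Step 2: residual SD, s, under three analyses.**

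- t test on t3 scores: s = 1
- t test on change scores: s = √(2 − 2r) = 1.183 / 1.000 / 0.775
- t3 scores adjusted for t0 (ANCOVA): s = √(1 − r²) = 0.954 / 0.866 / 0.714

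The change-score variance exceeds the ANCOVA variance by (2 − 2r) − (1 − r²) = (1 − r)², which is never negative. The t3-score variance exceeds it by r², also never negative. So in this large-sample comparison adjustment is at least as precise as either form of t test.

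**Step 3: power.** Power = Φ(d / (s × √(2/n)) − 1.96). For t3 scores with n = 253, this is Φ(0.25 / 0.0889 − 1.96) = Φ(0.852) = 0.803. For ANCOVA at r = 0.5, it is Φ(2.812 / 0.866 − 1.96) = Φ(1.287) = 0.901.

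| Analysis | n per arm | r = 0.3 | r = 0.5 | r = 0.7 |
|---|---|---|---|---|
| t3 scores | 253 | 0.80 | 0.80 | 0.80 |
| Change scores | 253 | 0.66 | 0.80 | 0.95 |
| Adjusted for t0 | 253 | 0.84 | 0.90 | 0.98 |
| t3 scores | 77 | 0.34 | 0.34 | 0.34 |
| Change scores | 77 | 0.26 | 0.34 | 0.52 |
| Adjusted for t0 | 77 | 0.37 | 0.43 | 0.58 |

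Leaving the baseline out of a t3 comparison costs about 4 to 17 percentage points of power at 253 per arm and about 3 to 24 at 77 per arm. These figures treat the planned numbers after dropout as complete data and do not model the imputation.

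**The case against.** **The article does not say that the baseline is ignored.** This is correct. A t test on t0-to-t3 change is not excluded, and the hypothesis could be read as pointing to one. But neither the analysis sentence nor Table 3 indicates it, and Step 2 shows that a change-score test would also be less precise than adjustment. At r = 0.3 it is worse even than the plain t3 comparison.

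**Text and table agree with each other.** The analysis section follows Table 3's division between changes and differences, so there is no contradiction between the two. The mismatch is with the four measurement points and with the hypothesis.

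**An article may leave such detail to the full protocol or analysis plan.** That covers the unnamed time point. It does not cover the method, which the article assigns to goal intention by name.

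**The numbers are borrowed.** This stands. The effect size belongs to another outcome, r is assumed, and the gain is computed for baseline adjustment only. It does not carry over to a plain difference-in-change model, so simply moving goal intention into the mixed model as written would not guarantee it.

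**A reader might infer that the t tests use completers only, given 50% dropout.** The article does not support this. The Summative evaluation section sets intention to treat with all randomised participants, and the section on sensitivity analysis and missing values imputes outcome variables in the ITT analysis if data are missing at random or completely at random. Only the per-protocol set requires complete outcomes. The condition on the imputation applies to every outcome.

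**A reader might also infer that goal intention is treated unlike every other secondary outcome.** That is too broad. Perceived goal attainment gets a t test as well, and the wording presents the two only as examples.

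**Conclusion.** The point holds in limited form. Goal intention has a t0 value in all three RCTs, is named for a between-group t test together with an outcome that has none, and on the natural reading its baseline is not used. This fits poorly with the hypothesis of a difference in change.

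The loss is one of precision on a single-item secondary outcome. It should not be read as bias: under randomisation an unadjusted t test is unbiased, and its standard error already covers chance imbalance at baseline. No primary result and no sample size is affected.

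The size depends on the assumed r and on d = 0.25. The direction does not depend on d: for any non-zero r below 1 and equal SDs, adjustment is more precise than either form of t test.

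**What to change.** In the Summative evaluation section, take goal intention out of the t-test sentence. State that it will be compared between groups at t3 with adjustment for its t0 value, either by ANCOVA or by a mixed model of t1 to t3 with t0 as a covariate, in the ITT set with the imputation already planned. The adjustment text at present names the baseline of the primary outcome only, so the t0 value of goal intention has to be named here. With equal expected baselines under randomisation, the adjusted group difference at t3 also addresses the hypothesis on change.

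Keep the comparison without baseline for perceived goal attainment, and name its time point. Change the Table 3 entry for goal intention to match.

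The cost is one or two sentences and one table cell. No new data are needed, since the t0 item is already in the questionnaires.
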